## Abstract

**Background:**

Anterior cruciate ligament (ACL) rupture is a devastating injury for most individuals, especially in athletes with the desire to go back to pivoting sports. In ACL reconstruction (ACL-R), multiple autograft options are available, each with distinct advantages and limitations. The quadriceps tendon (QT) autograft has gained increasing attention due to its favorable biomechanical properties and lower donor site morbidity, yet studies comparing only athletic populations remains limited. This study protocol describes a randomized controlled trial (RCT) aiming to compare QT autograft with bone-block (QT-B) with semitendinosus tendon (ST) autograft in athletes undergoing primary ACL-R.

**Methods:**

This is a single center RCT. Two Hundred ACL-R patients aged 16–40 years with a Tegner Activity Scale (TAS) of ≥ 7 prior to the ACL injury will be randomized to receive either a ST graft or a QT-B graft at the time of ACL-R. All participants will receive standard postoperative care and rehabilitation, followed by comprehensive follow-up. The primary outcome was the side-to-side (STS) difference in anterior tibial translation (ATT) at 6 months. Secondary outcomes include patient-reported outcome measures (PROMs), isokinetic strength testing, imaging-based graft evaluation, surgical and clinical events, and 10-year radiographic evidence of joint degeneration. Detailed definitions and timepoints are provided in the full manuscript (Table 1).

**Discussion:**

This protocol is the first RCT comparing the ST autograft to the QT-B autograft exclusively in athletes with TAS ≥ 7 undergoing ACL-R. In addition, this trial has the ambition of including 200 patients, thereby making it the largest trial to compare these two grafts to date. The successful completion of the trial has the potential to change current practice and contribute to the existing knowledge regarding graft choice in athletes undergoing ACL-R.

**Trial registration:**

The trial is registered at ClinicalTrials.gov: NCT04295148.

Registered date: 4 Mar 2020 (retrospectively registered).

## Background

Anterior cruciate ligament (ACL) ruptures are one of the most feared and potentially career-ending injuries for athletes. A recent Swedish study reported that female athletes may experience up to a 24-fold higher incidence of ACL reconstruction (ACL-R) compared to females in the general population, and male athletes up to a ninefold increase [1]. For those aiming to return to high-demand pivoting sports or activities, ACL-R is typically recommended as the preferred treatment to enable a safe and effective return to sports. The primary objective of surgical treatment with ACL-R is to restore anterior knee laxity [2], which can objectively be assessed by measuring anterior tibial translation (ATT) with an arthrometer such as KT-1000 [3]. Assessment of ATT using the KT-1000 arthrometer is best performed through the side-to-side (STS) difference, which is the standard method for detecting clinically relevant knee laxity and has demonstrated reliable and reproducible measurements for evaluating outcomes after ACL reconstruction [4].

The most common choice of graft for ACL-R in Sweden and worldwide is the hamstring tendon (HT)autografts, more particularly the semitendinosus tendon (ST) autograft [5, 6]. Bone-patellar tendon-bone (BPTB) autografts are another well-known and frequently used option. BPTB autografts have been associated with lower rates of graft failure and anterior knee laxity, but carry a higher risk of anterior knee pain, kneeling discomfort, and donor-site morbidity [7, 8]. In contrast, HT autografts typically result in less anterior knee pain and fewer harvest-site complications, although they have been associated with greater postoperative ATT and higher graft failure rates compared to BPTB [9, 10]. Despite these biomechanical concerns for HT autografts, recent evidence suggests that isolated semitendinosus (ST) grafts are less prone to increased laxity and are not significantly affected by factors such as graft diameter [11, 12].

Interestingly, the quadriceps tendon (QT) autografts yields comparable clinical and functional outcomes to both HT and BPTB autografts but with certain unique advantages [13, 14]. Notably, QT autografts have been associated with reduced incidence of anterior knee pain and kneeling discomfort compared to BPTB grafts, two common complaints after ACL-R with BPTB grafts [15, 16]. Moreover, QT autografts might offer the lowest donor-site morbidity among the three autografts (HT, BPTB and QT grafts), making it an interesting option to use [17].

The quadriceps tendon (QT) can be harvested either as an all–soft tissue graft (QT-S) or with a patellar bone block (QT-B). QT-B offers the theoretical advantage of bone-to-bone healing, potentially improving graft incorporation and stability, although there is a risk of complications such as patellar fracture. In contrast, QT-S avoids bone harvest and may be more suitable in certain patient groups, such as skeletally immature individuals [18, 19]. Recent systematic reviews and registry studies have reported comparable clinical outcomes between QT-B and QT-S [18, 19], although QT-B remains the more frequently studied QT autograft [20].

High quality registry studies have also provided conflicting evidence on whether QT grafts are associated with higher revision rates. In the Danish Knee Ligament Reconstruction Registry there have been reports that the revision rate for QT autografts was higher than that for HT and BPTB grafts; however, these findings have later been shown to only implicate cases where surgeons with less experience using the QT autografts have performed the ACL-R, emphasizing the importance of surgical expertise and proper technique in achieving optimal outcomes [21, 22].

Several randomized controlled trials have compared QT-B and HT grafts, showing no significant differences in knee laxity or subjective outcomes at 12 and 24 months postoperatively [13, 23, 24]. However, other functional outcomes will differ and are also clinically relevant when comparing QT and HT autografts. Both rehabilitation and muscle strength recovery after ACL-R will be affected by the graft type chosen for the procedure. For example, individuals undergoing ACL-R with QT graft have greater knee flexion strength but lesser knee extension strength compared to HT grafts [24, 25]. Likewise, isokinetic quadriceps strength measurements at 7 months have shown that patients undergoing ACL-R with QT grafts have impaired isokinetic quadriceps strength compared to HT and BPTB grafts [26]. Quadriceps strength after ACL-R with QT grafts often remains suboptimal for up to 24 months, which could be a reason for delay of return to sport. However, hamstring strength recovery is consistently better preserved with QT grafts than with HT grafts. Therefore, the rehabilitation protocol should be customized to address these deficits, prioritizing adequate quadriceps recovery to reduce the risk of reinjury while taking advantage of the hamstring strength preservation provided by QT grafts [27].

While the existing literature provides valuable insights into the outcomes of QT and HT grafts, a large RCT comparing ST and QT-B autografts in athletes with extended follow-up in a large range of outcomes measures, such as objective knee laxity and patient reported outcome measures (PROM) is essential to add to the current knowledge about the optimal graft choice for athletes.

This protocol has been prepared following the Standard Protocol Items: Recommendations for Interventional Trials (SPIRIT) 2013 Statement to ensure transparency, comprehensiveness, and adherence to best practices in protocol development [28].

## Methods

### Objectives

The primary aim of this study is to investigate potential differences in STS knee laxity at 6 months after ACL-R performed with either a ST graft or a QT-B graft in athletes with Tegner Activity Scale (TAS) ≥ 7 [29]. Patients will be followed for 6 months post ACL-R for the primary endpoint. Various secondary outcomes will also be measured to enable comprehensive evaluation of both short- and long-term outcomes.

### Hypothesis

For primary outcomes, it is hypothesized that 1) there will not be any significant differences in STS knee laxity at 6 months.

Further, for secondary outcome, it is hypothesized that 2) deficits in the isokinetic knee extension and flexion strength will differ between the choice of graft, 3) no differences in hop test LSIs will be observed, 4) no differences in frequently used PROMs after ACL-R will be noted, 5) no differences in return to sports rates, 6) nor differences in graft site morbidity will be seen.

Finally, it is hypothesized that 7) no differences in graft failure or contralateral ACL rupture will be observed, and that 8) the incidence of radiographic or symptomatic (PROMs) osteoarthritis at 10 years will be similar across both grafts.

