### Sample size calculation

To ensure adequate power, the sample size is based on Capio Artro Clinic’s clinical registry database from KT-1000 anterior knee laxity measurements available at the time of study planning, which indicated a standard deviation (SD) of 2.3 mm. This database includes over 7000 ACL-R and has served as the source to study postoperative knee laxity, functional test and graft comparisons [10–12, 30–32]. The power analysis is structured as follows: a 5% significance level, 80% power, and a minimum detectable difference of 1 mm in KT-1000 anterior knee laxity measurements. Based on these parameters, a minimum of 85 participants per group will be required as adequate sample. To account for potential dropouts, the sample size will be increased by 15%, resulting in 100 participants per group or 200 in total [33]. Recruitment will continue until each group has 100 fully evaluable participants for primary outcome measures.

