#### Graft failure, revision ACL-R and other adverse events

Participants will be followed longitudinally for a period of 10 years to monitor ACL graft failure (recurrent instability requiring revision), ACL re-rupture rates, and other adverse event affecting outcome (contralateral ACL rupture, infection or septic arthritis, bleeding, and any reoperation performed during the study period). Clinical and surgical records will be reviewed, and participants will be contacted periodically according to Table 1 to assess their knee health and report any additional surgeries or injuries. This long-term follow-up aims to evaluate the durability of ACL-R and identify factors associated with graft failure and re-rupture, such as patient demographics, activity levels, or surgical techniques. At the 5- and 10-year follow-ups, any undocumented events will be retrospectively collected via the Swedish National Knee Ligament Register (SNKLR).

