Categorical outcomes will be analyzed using Pearson’s chi-square or Fisher’s exact tests. Logistic regression may also be used to adjust for potential confounders when analyzing binary outcomes. Time-to-event outcomes, such as graft failure and return to sport, will be analyzed using Kaplan–Meier survival curves and Cox proportional hazards regression models, assuming the proportional hazards assumption is met.

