Following various outcome after ACL-R over time in both QT-B and ST autograft groups is also crucial for assessing short-term and long-term consequences of graft selection. Functional tests and RTS may provide insight into the early recovery and performance, while graft failure or contralateral injury reflects the durability and risk of new injuries. Although this trial is not designed to evaluate long-term outcomes, it may provide some insights into the long-term effects of different autografts in athletes aiming to return to sport.

Study limitations include the unblinded design for patients that were deemed unfeasible, for both orthopaedic surgeons and physiotherapists involved in patient care. Additionally, loss to follow-up and missing data are potential risks in prospective studies that the study team intends to minimize and that will be accounted for in data analysis. While this study focuses on patients with a TAS ≥ 7 with the desire to go back to the same level of sport, this subgroup was selected due to the sporting demands placed on the ACL graft. We do not claim that findings will universally apply to all ACL patients, and we understand that this may limit generalizability to lower-activity populations. However, we aim to generate insights that may contribute to evidence-based clinical decision-making and graft selection in athletic populations. Another limitation is that neither preoperative nor postoperative rehabilitation will be formally monitored or recorded. However, both follow standardized protocols routinely applied in our clinical practice.

Finally, the decision not to stratify randomization by sex could introduce imbalance between groups. However, the use of simple randomization is considered methodologically sound, with minimal risk of meaningful imbalance when sample sizes are 200 participants or larger [34, 60]. We plan to adjust for important covariates in the statistical analysis if imbalances are observed at baseline [60].

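### Hypotheses 7 and 8 predict sameness in graft failure, contralateral rupture and osteoarthritis, but with difference tests, no margin and a sample sized only for 6-month laxity, a non-significant result cannot support them

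*Protocol article*

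**What the plan says.** Hypothesis 7 in the Hypothesis section is that "no differences in graft failure or contralateral ACL rupture will be observed". Hypothesis 8 is that "the incidence of radiographic or symptomatic (PROMs) osteoarthritis at 10 years will be similar across both grafts". Neither comes with a margin, and similarity is not defined.

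For the analysis, the Statistical analysis section states: "Time-to-event outcomes, such as graft failure and return to sport, will be analyzed using" Kaplan–Meier curves and Cox regression. Categorical outcomes get Pearson's chi-square or Fisher's exact test, with logistic regression as an option. All the tests named are tests of difference.

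The sample size section covers one outcome only. It uses "a 5% significance level, 80% power, and a minimum detectable difference of 1 mm in KT-1000 anterior knee laxity measurements", with database information "which indicated a standard deviation (SD) of 2.3 mm". It gives 85 per group, raised to 100 for dropout. No event rate, event count or power is given for graft failure, contralateral rupture or osteoarthritis.

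On purpose, the section on graft failure and adverse events says "This long-term follow-up aims to evaluate the durability of ACL-R", with monitoring over 10 years. The Discussion qualifies this: "Although this trial is not designed to evaluate long-term outcomes", it may offer some insight into them.

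**The concern.** A prediction of no difference is not tested by a test of difference. Failing to reject means only that the data are compatible with no effect. They may be equally compatible with a large one, and the smaller the trial, the more likely it is to end that way. Pairing a sameness hypothesis with a difference test therefore makes low power work in the hypothesis's favour.

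For the primary outcome the protocol at least states the difference it is powered to find. For hypotheses 7 and 8 it states nothing of the kind: no margin, no event rate, no power and no role for confidence limits.

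Durability is a live question. The Background describes conflicting registry findings on revision after quadriceps tendon grafts. It adds that the excess was later traced to surgeons with less experience of that graft. If a non-significant result on failure were read as confirming hypothesis 7, athletes and surgeons could take the grafts to be equally durable when the data had not excluded a substantial excess.

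**Working it through.** **Step 1. The plan's own sample size.** Inputs from the Sample size calculation section: SD 2.3 mm, difference 1 mm, 5% level (taken as two-sided), 80% power.

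n per group = 2 × 2.3² × (1.96 + 0.8416)² / 1² = 2 × 5.29 × 7.849 = 83.04, so 84. The plan says 85, which agrees within rounding and small-sample correction. Dropout: 85 / (1 − 0.15) = 100. The stated figures reproduce. The t-test power for 1 mm is 0.805 at 85 per group and 0.864 at 100, so the laxity calculation is sound. It says nothing about event outcomes.

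**Step 2. Power for a doubling of graft failure.** The article gives no failure rate, so the lower-arm cumulative rate *p* is an assumption, ranged from 3% to 20%. The comparison is *p* versus 2*p* with 100 per group, two-sided 5%, no loss to follow-up. Chi-square and Fisher powers are exact binomial enumerations. Cox power is Φ(ln 2 × √D / 2 − 1.96), where D is the expected number of events at a hazard ratio of 2: D = 100 × [*p* + 1 − (1 − *p*)²].

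| Lower vs doubled rate | Chi-square | Fisher | Cox, HR 2 (events) |
|---|---|---|---|
| 3% vs 6% | 15% | 9% | 18% (9) |
| 5% vs 10% | 27% | 19% | 27% (15) |
| 8% vs 16% | 42% | 34% | 39% (23) |
| 10% vs 20% | 52% | 44% | 46% (29) |
| 12% vs 24% | 61% | 54% | 53% (35) |
| 15% vs 30% | 73% | 67% | 62% (43) |
| 20% vs 40% | 88% | 84% | 74% (56) |

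The first two columns are proportions. The Cox column uses a hazard ratio of 2, which gives slightly less than a doubling of cumulative risk. Power crosses 50% at a lower-arm rate of about 10% for chi-square and about 11% for Fisher or Cox. With 85 per group the chi-square figures for the first four rows are 13%, 23%, 36% and 45%.

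Events needed for 80% power at a hazard ratio of 2 (Schoenfeld, 1:1): 4 × (1.96 + 0.8416)² / (ln 2)² = 4 × 7.849 / 0.4805 = 65.3, so 66.

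**Step 3. What a null-looking result would exclude.** With D events split evenly and an observed hazard ratio of 1, the upper 95% limit is exp(1.96 × 2 / √D).

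- D = 10 (5% overall failure in 200 patients): exp(1.240) = 3.45
- D = 20 (10%): exp(0.877) = 2.40
- D = 30 (15%): exp(0.716) = 2.05

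Even a perfectly equal observed result would not exclude a doubling at up to 30 events.

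**Step 4. Osteoarthritis.** Assumed 20% versus 30%, 100 per group. Pooled rate 25%; null SE = √(2 × 0.25 × 0.75 / 100) = 0.0612; alternative SE = √((0.20 × 0.80 + 0.30 × 0.70) / 100) = 0.0608. Power = Φ((0.10 − 1.96 × 0.0612) / 0.0608) = Φ(−0.33) = 37%. From a 30% or 40% base, a 10-point difference has 32% or 29% power. A 20-point difference from a base of 20%, 30% or 40% has 88%, 83% or 81% power.

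**The case against.** Four points can fairly be made in defence of the plan.

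- **The power depends on an unstated rate.** A reader might infer that this trial would usually miss a doubling of graft failure. The article does not support that. Follow-up is 10 years in athletes who intend to return to their sport, so a cumulative rate above 10% cannot be ruled out. At 15% versus 30% or 20% versus 40%, a doubling is detected more often than missed. The argument about doublings also does not transfer to osteoarthritis: if that outcome is common, large differences are well covered and only moderate ones are not. This stands, and it is why the size is given as a range.
- **No passage says that p > 0.05 will count as proof of sameness.** The hypotheses are expectations, and a Cox model can yield a hazard ratio with its interval. To call a null result uninformative would therefore be too strong; it would be imprecise. A separate analysis plan may also contain reporting rules. This stands as far as it goes, but the hypotheses and the named tests are both printed here, and they do not fit each other.
- **The limit is disclosed.** The Discussion concedes that long-term outcomes were not what the trial was designed for. A reader might see a contradiction with the durability aim. It is better described as uneven wording, since secondary follow-up aims often go beyond what a trial is sized for. Still, the concession does not reach the Hypothesis section.
- **Losses may be small for failure events.** Recruitment runs until 100 per group are evaluable for the primary outcome, and the national register fills in missed events at 5 and 10 years. This is reasonable, so the main figures use 100 per group.

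**Conclusion.** The point holds in this form: hypotheses 7 and 8 are sameness claims, the planned analyses can show only difference, no margin is set, and the trial is sized for 6-month laxity alone. A non-significant result therefore cannot support either hypothesis. That conclusion needs no assumed rate.

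The size does. Over lower-arm failure rates of 3% to 20%, with 100 per group and no losses, chi-square power for a doubling runs from about 15% to 88%. At 10 to 30 events and an observed hazard ratio of 1, the upper confidence limit is 3.5 to 2.05. For osteoarthritis, 20% versus 30% has about 37% power. The rates are assumptions, not figures from the article.

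This is a matter of how secondary hypotheses are framed and reported. It does not touch the laxity sample size, which reproduces.

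**What to change.** Three changes of wording:

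1. **Hypothesis section.** Restate 7 and 8 as exploratory estimation aims, for example: The difference between grafts in graft failure, contralateral ACL rupture and 10-year osteoarthritis will be estimated as a hazard ratio or risk difference with its 95% confidence interval.
2. **Statistical analysis section.** Add: A non-significant test on these outcomes will not be reported as absence of a difference; the confidence limits will be used to state the largest excess risk not excluded.
3. **Graft failure and adverse events section.** Bring the durability aim into line with the limit already stated in the Discussion.

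A margin-based rule is not proposed. It would sit badly with an exploratory label, and with 10 to 30 events a hazard-ratio margin of 2 would be met only 19% to 48% of the time even if the grafts were identical: Φ(ln 2 × √D / 2 − 1.96).

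The change needs no extra patients, visits or data. It can be made before the primary analysis, expected in the second half of 2026 or early 2027, and well before the 10-year data. The cost is that the trial gives up a claim of equal durability that it is not sized to support.

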### Study design

This is a single-center prospective randomized controlled trial.

### Participants

The study will take place at the Capio Artro Clinic, Stockholm, Sweden, a highly specialized orthopedic clinic performing over 1000 ACL-Rs annually. The recruitment of the study participants will be performed at the outpatient department once inclusion and exclusion criteria have been checked. The TAS level will be assessed by the orthopedic surgeon responsible for patient enrolment into the study. The patients meeting inclusion criteria will be informed about the study and will be asked to participate. During the outpatient visit they will be handed the written consent form by the orthopedic surgeon and will later be randomized by an independent researcher, not directly involved in the study. All participants will undergo a standardized preoperative rehabilitation program prior to ACL-R. Data collection for the primary outcome will continue for two years.

Inclusion criteria:Age 16 −40 yearsPre-injury TAS ≥ 7Intended return to sports to prior sport and TAS LevelTime between injury and inclusion not more than 6 monthsMR verified ACL rupture

Exclusion criteria:Previous knee injury with symptoms before ACL injuryNeurological disease, inflammatory disease, connective tissue disease or balance disorderPrevious lower limb fracture or surgeryLaxity in the medial collateral ligament (MCL) and lateral collateral ligament (LCL) < grad 1Posterior cruciate ligament (PCL) rupture or Multiligament knee injury (MLKI)Radiographic sign of osteoarthritis (OA)Previous knee surgery or ligament injury in contralateral kneeBeighton score ≥ 5

